**Fig. 1 Fig1:**
[figure not shown]
Research process. TBLB, transbronchial lung biopsy; TBCB, transbronchial lung cryobiopsy; ROSE, rapid on-site evaluation

### Process of TBCB/TBLB

The patients enrolled will undergo both TBLB and TBCB procedures.

Tracheal intubation, mechanical ventilation, and vital signs monitoring

Sedation and analgesia. Place the bite and No. 8 tracheal catheter under the guidance of a soft bronchoscope. When the distal end of the catheter is located in the middle and lower part of the trachea, the catheter will be fixed. A monitor will monitor the vital signs.

(2)Placement of guide wire

Insert the soft bronchoscope via the nose, enter the trachea through the glottis from the trachea catheter, empty the capsule, and then enter the bronchus. Place the guide wire into the bronchus of the intended biopsy segment through the bronchoscope working passage, and exit the bronchoscope after the catheter is in its place. Fill the capsule and fix the guide wire, and then the guide wire will be strengthened by the respiratory therapist who is responsible for mechanical ventilation so that it will not displace.

(3)Placement and testing balloon

When the soft bronchoscope enters the airway through the tee and tracheal catheter, the assistant will send the balloon via the guide wire into the bronchial opening of the proposed biopsy segment or lobe. The balloon will be filled with air under direct vision and adjusted to completely close the bronchial opening of the proposed biopsy segment or lobe, and it is appropriate to remember the amount of air injected.

(4)TBCB/TBLB

When the endotracheal intubation is connected to the ventilator or high-frequency ventilation, bronchoscopy will be performed. First, conventional TBLB will be performed with biopsy forceps under the guidance of X-ray, and biopsies will be performed through different segmental bronchi 2 or 3 times in general. The biopsy specimens will be checked by pathologists and performed ROSE on site to guarantee the quality to continue the biopsy. After the biopsy, X-ray fluoroscopy will be performed to check whether there is pneumothorax, and the size of biopsy specimens, bleeding, pneumothorax and operation duration will be recorded. Then, TBCB will be performed at the same site. Freezing probes will be sent to the biopsy site through a bronchoscope work channel with positioning. The bronchoscope and cryogenic probe will be pulled out after refrigeration at a distance of 1 ~ 2 cm away from the pleura for 3 ~ 4 s. Take the biopsy specimen off after thawing. The bronchoscope will reenter into the bronchial to check for bleeding. Biopsy is usually done 2 ~ 3 times. Figure 2 shows the lung tissue obtained by TBCB. Biopsy specimens will be checked by pathologists and will be performed ROSE on site to guarantee the quality for further biopsy. After the biopsy, X-ray fluoroscopy will be performed to check for pneumothorax, and size of the biopsy specimen, bleeding, pneumothorax condition and operation duration will be recorded. In both operations, the next biopsy will be performed in the absence of significant bleeding and pneumothorax. To do another site of biopsy, insert a guide wire into the balloon again, and guide the balloon into the new segment by clamping the guide wire with biopsy forceps, and repeat the preceding process. After the biopsy, mechanical ventilation and tracheal intubation will be removed when the patient regains consciousness, and the patient will be sent back to the ward for monitoring and observation for 4–6 h.

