## Methods

### Study objects

According to the literatures, the estimated sensitivity rates of TBCB and TBLB methods were 80% and 60%, respectively. The estimated prevalence rate of the target subjects is 50%. Using McNemar test with PASS software to calculate the sample size, when the value of ɑ was 0.05, the sample size was 122 cases. And totally 146 hospitalized patients with diffuse lung disease were intended to be enrolled in the study with the amplification of 1.2 times. The specific criteria are as follows:Inclusion criteria

(a) ILD patients with unknown reasons (more than 18 years old), have the necessity to undergo TBCB for the diagnosis; (b) Hospitalized patients need to complete arterial blood gas analysis, blood routine, blood coagulation routine, liver and kidney function, electrocardiogram, immunology examination, chest HRCT, and other examinations; (c) Good compliance and can be coordinated with this study; (d) After being fully informed of the purpose and method of the study, the patients are willing to participate in the study and sign the informed consent.

(2)Exclusion criteria

(a) Do not agree to participate in the study; (b) Have participated in other studies that could affect the observation of this study; (c) Patients who fail to complete the examination required for admission before TBCB or TBLB; (d) Chest HRCT showed non-interstitial lung disease; (e) Any conditions deemed unsuitable for inclusion by the investigators;

(3) Elimination criteria

(a) Patients who do not meet the inclusion criteria or who meet the exclusion criteria after enrollment; (b) After enrollment, patients have poor compliance and could not cooperate with the observers;

(4)Withdrawal criteria

Patients who meet the inclusion criteria and fail to complete the study for some reasons, including patients who voluntarily withdraw and are determined to withdraw by the researchers.

(5)Study end pointsa. Primary end point: The differences in diagnostic efficiency and incidence of operation-related complications between TBCB and TBLB.b. Secondary end point: Analyze the relationship between the time of biopsy and the incidence of complications; the relationship between freezing time, size of specimen and complications; The histopathological results will be handled in a multidisciplinary meeting, to analyze the consistency of pathological, clinical, and radiology.

The research process is shown in Fig. 1.

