***Collection of clinical data***

Collect relevant information about the operation, including anesthesia method, anesthesia complications, time of TBCB, time of TBLB, freezing time, and operation time;Specimens’ information, including the number and size of specimens, ROSE results, and pathological results;Complications caused by the operation, including bleeding, pneumothorax, infection, and acute exacerbations caused by the operation, as well as the delayed complications mentioned above during the 3 days of follow-up after the operation.Collecting adverse events in the study:

iii.a. Adverse event (AE): Any adverse medical event that occurs during the observation period of a patient during the study, which does not necessarily imply a causal relationship with the procedure.iv.b. Serious adverse event (SAE): An adverse event meeting one or more of the following criteria is considered as SAE, such as death; life threat; persistent or severe disability or permanent loss of function; hospitalization or prolonged stay due to AE; leading to congenital malformation.v.c. Severity classification of adverse events: mild——uninduced or only causing mild discomfort, not affecting daily life and not requiring clinical management; moderate——active narration, affecting daily life, but tolerating, requiring clinical general management; severe——having objective manifestation that cannot be tolerated, surely affecting daily life, needing rest in bed and active clinical treatment.vi.d. Relationship between adverse events and operation: it can be divided into five levels: ① definitely relevant, ② probably relevant, ③ possibly relevant, ④ probably irrelevant, and ⑤ definitely irrelevant. ①, ②, ③ are considered as operation-related adverse events.

(5) Severity of bleeding

Grade 0: no bleeding; Level 1: bleeding that can be stopped by negative pressure suction without other hemostatic measures; Level 2: bleeding that requires local injection of frozen saline, epinephrine, or balloon closure; Level 3: severe bleeding that beyond endoscopic control, resulting in hemodynamic and respiratory instability, requiring vascular intervention or surgical hemostasis, or requiring admission to intensive care unit (ICU).

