About the safety of TBCB, it was reported that there were no significant differences in the incidence of pneumothorax, bleeding, and bleeding severity compared with conventional TBLB [20, 21]. Yarmus et al. [22] reported for the first time that TBCB was used to evaluate 11 patients after lung transplantation under a soft microscope and achieved satisfactory results without serious complications. The CHILL study [23] reported that TBCB was associated with mild bleeding (grade 1 bleeding that requiring suction to clear) in 56.2% of patients, but only 16 cases were included in the study. These studies indicated that TBCB had good safety and efficacy in ILD, but they were all retrospective studies with small samples, and prospective studies with large samples are urgently needed in clinical practice to evaluate the diagnostic value of TBCB in ILD.

ROSE is a rapid cytological interpretation technique which accompanies sampling in real time during diagnostic interventional operations. In the sampling of the target sites, under the premise of almost no loss of tissue specimen, part of the sample is printed on the slides to make a cytological substrate, quickly stained and immediately interpreted with a special microscope integrated with clinical information. As a cell carrier, ROSE has the following functions: evaluation quality of the samples, guidance intervention means of operation in real time, forming the preliminary diagnosis or narrowing the scope of differential diagnosis, optimization the processing scheme of the target specimen, analyzing and predicting the outcomes of the disease combined with all clinical and cytological information [24]. However, ROSE has not been applied in ILD at present.

It is a prospective and self-controlled study to evaluate the diagnostic value of TBCB/TBLB combined with ROSE technology in a large sample size of ILD patients. In addition, it is the first time that ROSE technique was used in the diagnosis of ILD. The results of this study will clarify the value of TBCB in the diagnosis of ILD and confirm its safety and effectiveness, which is expected to improve the efficiency of diagnosis and improve the prognosis of ILD patients.

Abbreviations: TBLB, transbronchial lung biopsy; TBCB, transbronchial lung cryobiopsy; ROSE, rapid on-site evaluation.

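### The primary complication comparison covers delayed events that arise after both techniques at one site and cannot be attributed to either; immediate events can be compared only as TBLB first versus TBCB after TBLB

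*Protocol article*

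**What the plan says.** Under Study objects, item (5), the primary end point is given as "The differences in diagnostic efficiency and incidence of operation-related complications between TBCB and TBLB".

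Under Process of TBCB/TBLB, "The patients enrolled will undergo both TBLB and TBCB procedures". Item (4) fixes the sequence at a site: "First, conventional TBLB will be performed with biopsy forceps under the guidance of X-ray", and after the TBLB check, "Then, TBCB will be performed at the same site". The check after TBLB reads "After the biopsy, X-ray fluoroscopy will be performed to check whether there is pneumothorax, and the size of biopsy specimens, bleeding, pneumothorax and operation duration", all of which is recorded. An equivalent check and record follow TBCB. The same item lets the next biopsy go ahead only when there is no significant bleeding or pneumothorax, and has the whole process repeated when another site is sampled.

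Under Collection of clinical data, the complications are bleeding, pneumothorax, infection and acute exacerbation, "as well as the delayed complications mentioned above during the 3 days of follow-up after the operation". Relatedness is graded as follows: "Relationship between adverse events and operation: it can be divided into five levels". The top three levels count as operation-related.

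The Discussion calls the trial self-controlled: "It is a prospective and self-controlled study to evaluate the diagnostic value of TBCB/TBLB combined with ROSE technology".

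**The concern.** A self-controlled design suits the diagnostic comparison, because each technique yields its own specimen. It suits complications less well, because both techniques act on the same lung, at the same site, minutes apart. An event that first shows after both have been done carries no information on which one caused it.

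At stake is half of a two-part primary end point. The article expects the results to confirm the safety of TBCB. A between-technique safety statement that rested on delayed events would depend on a counting convention, whichever way it came out.

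**Working it through.** **Plan's own figures.** The article gives no complication rate on which the comparison was planned. Its sample size (122, and 122 × 1.2 = 146.4, stated as 146) rests on diagnostic sensitivity only. Below, 146 serves only to turn rates into counts.

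**Step 1: which events have a technique-specific record?**

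| Event | Recorded between TBLB and TBCB | Recorded after TBCB | Attributable to one technique |
|---|---|---|---|
| Immediate bleeding, pneumothorax | yes | yes | by phase of detection only |
| Delayed bleeding, pneumothorax (3 days) | no | yes | no |
| Infection | no | yes | no |
| Acute exacerbation | no | yes | no |

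**Step 2: what a convention does to delayed events.** Suppose all 146 patients have both techniques and D patients have a delayed event. Counted for both techniques, these add 0 to the difference. Counted for the last technique, they add D/146 against TBCB. Counted for the first, they add D/146 against TBLB. Each such patient moves the difference by up to 1/146 = 0.68 percentage points either way, by rule and not by observation.

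**Step 3: immediate events, late-showing TBLB injury (assumed rates).** Let p_T and p_C be the true risks, and u the share of TBLB events that show only after the first check and are then recorded in the TBCB phase. If every patient proceeds:

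- recorded TBLB = p_T × (1 − u)
- recorded TBCB = p_C + p_T × u

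With p_T = p_C = 5%, so that the true difference is 0:

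| u | Recorded TBLB | Recorded TBCB | Spurious difference |
|---|---|---|---|
| 0 | 5.0% | 5.0% | 0 points |
| 10% | 4.5% | 5.5% | 1.0 point |
| 25% | 3.75% | 6.25% | 2.5 points |
| 50% | 2.5% | 7.5% | 5.0 points |

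**Step 4: the condition for going on.** Suppose instead that patients with an event at the first check do not go on to TBCB. With r = 5% for both techniques and independent events, the recorded TBCB rate among those who proceed is 1 − (1 − r) × [1 − r·u / (1 − r(1 − u))].

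- At u = 25%: 1 − 0.95 × (1 − 0.0125/0.9625) = 6.23%. In 146 patients that is about 146 × 0.0375 = 5.5 TBLB events and 146 × 0.9625 × 0.0623 = 8.8 TBCB events.
- At u = 0: 146 × 0.05 = 7.3 TBLB events, but only 146 × 0.95 × 0.05 = 6.9 TBCB events. Divided by all 146, TBCB now looks slightly safer (4.75% vs 5.0%). Divided by the 138.7 expected to reach it, the rate is again 5.0%.

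So the denominator matters, and the distortion can change sign. If patients who bleed or leak at TBLB are also at higher risk at TBCB, the patients who proceed are a lower-risk group, which favours TBCB further.

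**Step 5: more than one site.** Repeating the process at a second site puts TBLB there after TBCB at the first. A late TBCB event from the first site could then be recorded in a TBLB phase.

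**The case against.** The strongest reply is that the article already separates the phases. Bleeding and pneumothorax are checked and recorded after TBLB and again after TBCB, the times of the two techniques are collected separately, and significant bleeding or pneumothorax stops the next biopsy. An attribution rule or a phase-of-onset field is the sort of detail that a full protocol, case report form or analysis plan may hold. This stands for immediate events, so a reader who inferred that the whole complication half of the primary end point cannot be estimated would go too far.

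A reader might also infer that TBLB events are charged to TBCB and that the comparison is therefore biased against TBCB. The documents do not support that. No attribution rule is stated, so charging to TBCB is only a possible result of the recording sequence. The condition for proceeding and multi-site sessions can push the other way. A 50% late share is an assumption at the unfavourable end of the range shown; at 10% the spurious difference is 1 point.

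Nor does the causality scale settle the matter. Operation may there mean the whole session, but the section on the procedure also uses the word for each technique. The wording is ambiguous.

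The reply does not reach events that first arise after both techniques. There the information does not exist, and no analysis plan or form can supply it.

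**Conclusion.** The point holds in two parts.

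First, infection, acute exacerbation and delayed bleeding or pneumothorax cannot be assigned to TBLB or TBCB, so a between-technique test that includes them is not interpretable. This follows from the stated design and needs no assumed rate.

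Second, immediate bleeding and pneumothorax can be compared, but the quantity estimated is TBLB done first versus TBCB done after TBLB at the same site. It is not the risk of TBCB on its own. Distortion of unknown size and direction is possible. The 1.0, 2.5 and 5.0 points above rest on an assumed equal 5% risk, assumed late shares of 10%, 25% and 50%, recording of late events in the TBCB phase, and all patients proceeding. That a wrong safety conclusion would follow is not shown; that one could follow is.

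Because a primary end point is affected, the wording should be settled early. Trial status reports one patient enrolled.

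**What to change.** - Restrict the primary between-technique complication comparison to immediate bleeding and pneumothorax, as recorded at the end-of-TBLB and end-of-TBCB checks.
- State the denominator for each technique as the number of patients who reached it, and label the TBCB rate as conditional on prior TBLB at the same site.
- Report delayed bleeding and pneumothorax, infection and acute exacerbation once per patient for the combined procedure, with a 95% CI and no TBCB-versus-TBLB test.
- Record phase of onset (TBLB, TBCB, after both) and site of onset on the adverse event form, so that multi-site sessions can be read.
- State that stand-alone TBCB complication rates are not estimated.

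The cost is a change to the end-point wording and two form fields. Most of the immediate data are already to be collected. The downside is a narrower safety claim. The order of the procedures is a clinical matter and is left unchanged.

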**Fig. 2 Fig2:**
[figure not shown]
Lung tissue obtained by transbronchial lung cryobiopsy

***Collection of clinical data***

Collect relevant information about the operation, including anesthesia method, anesthesia complications, time of TBCB, time of TBLB, freezing time, and operation time;Specimens’ information, including the number and size of specimens, ROSE results, and pathological results;Complications caused by the operation, including bleeding, pneumothorax, infection, and acute exacerbations caused by the operation, as well as the delayed complications mentioned above during the 3 days of follow-up after the operation.Collecting adverse events in the study:

iii.a. Adverse event (AE): Any adverse medical event that occurs during the observation period of a patient during the study, which does not necessarily imply a causal relationship with the procedure.iv.b. Serious adverse event (SAE): An adverse event meeting one or more of the following criteria is considered as SAE, such as death; life threat; persistent or severe disability or permanent loss of function; hospitalization or prolonged stay due to AE; leading to congenital malformation.v.c. Severity classification of adverse events: mild——uninduced or only causing mild discomfort, not affecting daily life and not requiring clinical management; moderate——active narration, affecting daily life, but tolerating, requiring clinical general management; severe——having objective manifestation that cannot be tolerated, surely affecting daily life, needing rest in bed and active clinical treatment.vi.d. Relationship between adverse events and operation: it can be divided into five levels: ① definitely relevant, ② probably relevant, ③ possibly relevant, ④ probably irrelevant, and ⑤ definitely irrelevant. ①, ②, ③ are considered as operation-related adverse events.

(5) Severity of bleeding

Grade 0: no bleeding; Level 1: bleeding that can be stopped by negative pressure suction without other hemostatic measures; Level 2: bleeding that requires local injection of frozen saline, epinephrine, or balloon closure; Level 3: severe bleeding that beyond endoscopic control, resulting in hemodynamic and respiratory instability, requiring vascular intervention or surgical hemostasis, or requiring admission to intensive care unit (ICU).

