### Statistical analysis

The original data will be uniformly stored in the paper version of the case report form, and the electronic data will be single-path input and checked by two researchers. The database will be input to Excel software and will be statistically analysed with SPSS 25.0 software. The measurement data of normal distribution will be expressed as X ± S, and the measurement data of skewness distribution will be expressed as M (P25, P75). The Mann-whitney U test will be used for comparison. Enumeration data will be expressed as cases and percentages, and chi-square tests will be used for comparison.

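### The primary complication incidence does not fix which bleeding level counts; as written it admits suction-only bleeding, which could dominate the rate and mask or distort a difference in more important complications

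*Protocol article*

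**What the plan says.** The section Study objects sets out the "Primary end point: The differences in diagnostic efficiency and incidence of operation-related complications between TBCB and TBLB". No severity threshold is given there.

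Collection of clinical data lists the events: "Complications caused by the operation, including bleeding, pneumothorax, infection, and acute exacerbations caused by the operation". Bleeding carries no grade. The same section defines a bleeding scale in which only Grade 0 means none, followed by "Level 1: bleeding that can be stopped by negative pressure suction without other hemostatic measures" and then Levels 2 and 3. It also says which causality levels "are considered as operation-related adverse events". That rule filters on cause, not on severity.

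Statistical analysis says: "Enumeration data will be expressed as cases and percentages, and chi-square tests will be used for comparison".

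The Discussion reports of one cited study that "TBCB was associated with mild bleeding (grade 1 bleeding that requiring suction to clear) in 56.2% of patients", and notes that it had 16 cases. Of earlier comparisons it says "there were no significant differences in the incidence of pneumothorax, bleeding, and bleeding severity compared with conventional TBLB".

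**The concern.** Biopsy causes Level 1 bleeding directly, so the causality rule would not remove it. Counted as cases and percentages, an ooze cleared by suction then weighs the same as Level 3 bleeding and, in any pooled rate, the same as a pneumothorax. If Level 1 is as common as the cited study suggests, most patients counted as having a complication could have nothing else.

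Two things are at stake. If Level 1 is about equally common under both techniques, it adds noise and can bury a difference in the events that matter. The Discussion expects the results to confirm safety, so a non-significant comparison is likely to be read that way. If Level 1 rates differ, the comparison may be significant because of minor bleeding alone, or may point the wrong way. Choosing a threshold after the data are seen would be a choice among results.

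**Working it through.** **The plan's own figures.** No figure is stated for the complication end point; the sample size rests on sensitivity only. The inflation reproduces: 122 × 1.2 = 146.4, given as 146. The 122 can be neither confirmed nor refuted, because power and discordance are not stated. The McNemar formula is n = (z_α√ψ + z_β√(ψ − d²))² / d², with d = 0.80 − 0.60 = 0.20. With ψ = 0.32, two-sided α of 0.05 and 80% power, it gives (1.960 × 0.566 + 0.842 × 0.529)² / 0.04 ≈ 60.4, so 61, and 61 / 0.5 = 122. With independence, ψ = 0.44 and the total is 168. None of this bears on the complication end point, except that 122 and 146 are the numbers of pairs available.

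**Inputs**
- Level 1 with TBCB: 56.2% (Discussion). This matches 9/16 = 56.25%; the exact 95% interval for 9 of 16 (quantiles of Beta(9,8) and Beta(10,7)) is 30% to 80%.
- Level 1 with TBLB: not given; assumed, and varied below.
- Important events (Level 2–3 bleeding, pneumothorax, infection, exacerbation): not given; assumed 5% with TBLB and 15% with TBCB.

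**Method.** Exact McNemar test, two-sided 0.05. With technique rates pL (TBLB) and pC (TBCB), independent within patient, the discordant probabilities are pC(1 − pL) and pL(1 − pC). Power is summed over the binomial number of discordant pairs.

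**Important events only.** The discordant probabilities are 0.15 × 0.95 = 0.1425 and 0.05 × 0.85 = 0.0425. Power is 68% with 122 pairs and 77% with 146.

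**Adding Level 1 at rate L in both techniques.** The any-event rate is 1 − (1 − L)(1 − s), where s is the important-event rate.

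| L | TBLB v TBCB | Power, n = 122 | Power, n = 146 |
|---|---|---|---|
| 20% | 24.0% v 32.0% | 24% | 29% |
| 30% | 33.5% v 40.5% | 17% | 20% |
| 56.2% | 58.4% v 62.8% | 8.5% | 10% |
| 80% | 81.0% v 83.0% | 5% | 5% |

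At L = 56.2%, the share of TBCB patients with an event who have Level 1 only is 0.562 × 0.85 / 0.628 = 76%.

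**Relaxing the assumptions (n = 122, Level 1 at 56.2% in both)**
- Level 1 and important events mutually exclusive: 56.2% + 5% = 61.2% v 56.2% + 15% = 71.2%; power 33%.
- Level 1 fully shared within patient: discordant probabilities 0.438 × 0.1425 = 0.062 and 0.438 × 0.0425 = 0.019; power 28%.

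**Unequal Level 1 rates (n = 122)**
- TBCB at 56.2% and TBLB at 50%, 45%, 40% or 30%: power 32%, 61%, 85% or over 99%.
- Important events equal at 10%, Level 1 at 30% (TBLB) v 56.2% (TBCB): 1 − 0.7 × 0.9 = 37.0% v 1 − 0.438 × 0.9 = 60.6%; power 95%, although important events do not differ.
- Important events 5% v 15%, Level 1 at 56.2% (TBLB) v 30% (TBCB): 58.4% v 40.5%, which favours the technique with more important events.

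**The case against.** A reader might infer that the protocol defines a composite counting any bleeding, and that this hides a real difference. The documents do not support that much.

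- **No composite is stated.** Four kinds of event are listed, and the Discussion treats pneumothorax, bleeding and bleeding severity as separate items. If events are compared one by one, pneumothorax is unaffected. This stands, but the bleeding rate would still mix Level 1 with Levels 2 and 3.
- **The protocol neither includes nor excludes Level 1 expressly.** This also stands; inclusion is the plain reading, not a written rule.
- **Masking is one scenario.** It needs similar Level 1 rates under both techniques, and no TBLB rate is given. The cited absence of significant bleeding differences makes similar rates plausible but does not establish them. The 56.2% comes from 16 cases.
- **The fall to 8.5% is near the worst case.** On a scale that gives each procedure one worst grade, Level 1 and Level 2–3 bleeding exclude each other. Both biopsies are also taken in the same patient, session and site, so independence is doubtful. Either change brings power back to around 30%. It does not follow that the comparison loses nearly all its power.
- **Grades are recorded, and such detail can sit in an analysis plan.** Graded reporting is indeed possible. But what counts as an event defines the primary end point itself, and nothing stated ties the incidence to a level.
- **Counting all bleeding and reporting it by grade is defensible.** Agreed, if that choice is made in advance.

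**Conclusion.** The point holds in a limited form. As written, the primary complication incidence admits Level 1 bleeding, and the protocol's only cited rate for it is high enough that it could dominate the bleeding rate and any pooled rate. The effect may be to mask a difference in important complications, to create one, or to reverse it; the documents do not show which.

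Under equal Level 1 rates of 56.2% and important events of 5% v 15%, power with 122 pairs falls from 68% to between 8.5% (everything independent) and 33% (grades mutually exclusive). Only the 56.2% and the number of pairs come from the protocol; the other rates are assumptions. No planned safety power is lost, since none was stated. This is an inexpensive improvement to the end point's definition, not a flaw that makes the safety comparison unusable.

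**What to change.** Before further enrolment:

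1. State which level of the protocol's own bleeding scale counts toward the primary complication incidence. Level 2–3 is one option; the choice belongs to the investigators.
2. Report each component and each bleeding level separately by technique.
3. Compare the recorded bleeding grade within patient with a paired ordinal test (Wilcoxon signed-rank or marginal homogeneity) in place of the stated chi-square test, which, as named, uses neither the pairing nor the order of the grades.

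The cost is a sentence of end-point wording and a line of analysis. The grades are already defined, bleeding is already recorded after each procedure, and Trial status reports only one patient enrolled. If Level 1 is left out, the headline rate has fewer events, and Level 1 differences appear only in the graded table.
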